## 6.4 Clinical Performance

All specimens will be tested in singlicate in a randomized blinded fashion.

The acceptance criteria for the performance as 95% agreement at 1000 ge copies / mL, and 100% agreement at all other higher concentrations and for negative specimens.

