## 1.2 WHO Performance Evaluation of YF Nucleic Acid Tests (NAT)

This document is intended to provide manufacturers of YF NATs and the WHO Evaluating Laboratory with the WHO performance evaluation procedure.

The protocol provides the details of the procedure for the laboratory-based performance evaluation of selected YF molecular assays (also referred to as nucleic acid tests and henceforth in this document as NATs) submitted for evaluation. It describes the procedures required to perform an evaluation of YF NATs submitted for evaluation. **This protocol is not intended to replace validation and verification studies that need to be conducted by the manufacturer.**

The evaluation verifies the performance characteristics of YF NATs, assessing their precision (reproducibility and repeatability), analytical sensitivity, and analytical specificity and clinical performance.

All assays will be performed using a commercially supplied quality control (QC) specimen, and a proficiency panel will be used by all analysts prior to performance evaluation.

Artificially prepared panels will be used to determine precision, inclusivity, analytical sensitivity and specificity. The clinical performance will be evaluated using specimens collected in a YF endemic region during a period of no outbreak. Given the non-availability of YF-positive serum specimens, clinical-like specimens will be generated by spiking serum with a range of concentrations of YFV grown in cell culture. In addition, operational characteristics of the assays will be evaluated, including ease of performance and suitability for use in laboratories within the YFLN.

Testing to evaluate the performance of the NATswill take place at a laboratory with recognised standards accreditation (traceable to ILAC)such as ISO 17025:2017 or ISO 15189:2012 for the performance of NATs.

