## 5.5 Clinical performance panel

- Left-over whole blood or serum submitted for routine testing can be used to evaluate the assays. Clinical specimens should be stored frozen at -20°C or preferable -80°C when available until testing. Total 100 specimens: 10 spiked with 5000 ge /mL of the African wild strain, 10 spiked with 5000 ge /mL of the South American wild strain and 80 non-reactive specimens will be tested.

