### Table 1: Assay Performance Specimen Reference Panel

| **Analyte - Sample type** | **Concentration (copies/mL)** | **N° of replicates** | **Total N° replicates** |
| --- | --- | --- | --- |
| **Precision of measurement and inclusivity** |  |  |  |
| **Intra-assay precision/inclusivity** |  |  |  |
| YF 17D vaccine strain* | Each strain will be diluted at a concentration of ca. 10^3^, 10^4^ and 10^5^ ge copies /mL and run in quadruplicate | 3 | 12 |
| African wild type strain* |  | 3 | 12 |
| South American wild type strain* |  | 3 | 12 |
| **Inter-assay precision** |  |  |  |
| YF 17D vaccine strain* | Each strain will be diluted at a concentration of ca. 10^3^, 10^4^ and 10^5^ ge copies /mL and run in quadruplicate on 3 different days by different technicians (day 1 can use intra-assay data) | 3 | 24 |
| African wild type strain* |  | 3 | 24 |
| South American wild type strain* |  | 3 | 24 |
| **Inter-lot variability** |  |  |  |
| YFV 17D vaccine strain* | Each strain will be diluted at a concentration of ca. 10^3^, 10^4^ and 10^5^ and run in quadruplicate | 3 | 12 |
| YFV African wild type strain* |  | 3 | 12 |
| YFV South American wild type strain* |  | 3 | 12 |
| **Analytical Sensitivity** | | | |
| YFV Standard preparation* | ca. 10, 50, 100, 500, 1000, 5000, 10^4^, 5x10^4^, 10^5^, 5x10^5^, 10^6^ , 5x10^6^ ge copies /mL** | 5 | 25 |
| **Analytical Specificity (**Flavivirus strain detection) | | | |
| Hepatitis C* virus | Medium concentration  ca. 10,000 ge copies/mL | 1 |  |
| Dengue 1, 2, 3, 4*virus |  | 1 |  |
| Zika virus* |  | 1 |  |
| West Nile virus* |  | 1 | 9 |
| Tick Borne Encephalitis virus* |  | 1 |  |
| Japanese Encephalitis virus* |  | 1 |  |
| **Analytical Specificity (other pathogens)** | | | |
| Ebola virus* | medium concentration  ca. 10,000 ge copies/mL | 1 |  |
| Lassa fever virus* |  | 1 |  |
| Marburg virus* |  | 1 |  |
| HIV* |  | 1 | 8 |
| Hepatitis E virus* |  | 1 |  |
| Chikungunya virus* |  | 1 |  |
| Measles virus* |  | 1 |  |
| Influenza virus* |  | 1 |  |
| **Analytical Specificity (interfering substances)** | | | |
| Haemoglobin | 200 g/L | 3 |  |
| Triglyceride | 5.6 mmol/L | 3 | 12 |
| Bilirubin (unconjugated) | 257 µMol/L | 3 |  |
| Malaria positive sera |  | 3 |  |
| **Clinical Performance Panel** | | | |
| Non-reactive serum specimens Spiked African wild type | 5000 ge copies/ mL | 10 | 10 |
| Non-reactive serum specimens Spiked South American wildtype | 5000 ge copies/ mL | 10 | 10 |

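### The clinical acceptance rule sets a criterion at 1000 ge/mL, but none of the 100 clinical specimens is at that level

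*Protocol*

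**What the plan says.** Section 6.4 (Clinical Performance) has the specimens tested once each, randomized and blinded, and then gives the pass rule in three clauses. The first two are "The acceptance criteria for the performance as 95% agreement at 1000 ge copies / mL, and 100% agreement at all other higher concentrations". The third extends the 100% requirement to the negatives.

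Section 5.5 fixes the panel: "Total 100 specimens: 10 spiked with 5000 ge /mL of the African wild strain", then "10 spiked with 5000 ge /mL of the South American wild strain and 80 non-reactive specimens will be tested". The clinical rows of Table 1 agree. Both spiked rows are at 5000 ge copies/mL with 10 specimens each, and the remaining row holds 80 unspiked specimens.

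Section 1.2 describes the spiked material differently: "clinical-like specimens will be generated by spiking serum with a range of concentrations of YFV grown in cell culture".

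Section 8.3 sets a separate analytical criterion, a limit of detection of at most 1000 ge copies/mL. An assay that misses it is not considered for listing.

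**The concern.** A pass rule and the panel it governs are both fixed in the protocol, and they do not match. The rule presumes specimens at 1000 ge/mL and at more than one higher level, and section 1.2 likewise speaks of several concentrations. Section 5.5 and Table 1 provide one level, 5000 ge/mL. A later analysis plan cannot repair this, because it cannot create specimens that the laboratory did not prepare.

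As written, the laboratory would have to ignore the first clause, borrow data from another panel, or choose a reading once results are known. Different assays could then be judged by different rules. The clause affected is also the one that would have tested detection of wild-type virus in clinical serum at the 1000 ge/mL limit.

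**Working it through.** **1. Tally of the panel (section 5.5, Table 1).** 10 African + 10 South American + 80 unspiked = 100, which reproduces the stated total.

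| Clause in section 6.4 | Specimens available | Can it be applied? |
|---|---|---|
| 95% at 1000 ge/mL | 0 | No |
| 100% at higher levels | 20 (all at 5000) | Yes |
| 100% for negatives | 80 | Yes |

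**2. What the usable clauses can show.** Section 8.4 specifies exact binomial intervals. For n successes in n, the two-sided 95% lower bound is 0.025^(1/n).
- 20/20: 0.025^(1/20) = 83.2%
- 10/10 (one strain): 69.2%
- 80/80: 95.5%

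**3. How well 5000 ge/mL separates assays.** With true detection p at 5000, the chance of 20/20 is p^20: 12.2% for p = 90%, 35.8% for 95%, 66.8% for 98% and 81.8% for 99%.

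To relate p to the detection limit I assume single-hit detection, p(c) = 1 − 0.05^(c/LoD95), where LoD95 is the concentration detected 95% of the time. The protocol gives no such curve, so this is an assumption. I show a range of LoD95.

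| LoD95 (ge/mL) | p at 5000 | P(20/20) |
|---|---|---|
| 2500 | 1 − 0.05^2 = 0.9975 | 0.9975^20 = 95% |
| 5000 | 0.95 | 0.95^20 = 36% |
| 10,000 | 1 − 0.05^0.5 = 0.776 | 0.776^20 = 0.6% |

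**4. What specimens at 1000 ge/mL would add.** With fewer than 20 specimens a single miss gives less than 95%, so the rule is the same as 100%. Twenty is the smallest number that allows one miss (19/20 = 95%). P(≥19/20) = p^20 + 20(1 − p)p^19.

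| LoD95 (ge/mL) | p at 1000 | P(≥19/20) |
|---|---|---|
| 500 | 0.9975 | 99.9% |
| 1000 | 0.95 | 0.358 + 0.377 = 74% |
| 2500 | 1 − 0.05^0.4 = 0.698 | 0.7% |

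**5. Where else about 1000 ge/mL is tested.**
- *Precision panel (Table 1, section 6.2).* Each strain at 10^3, in quadruplicate over three runs plus a second lot: 4 × 3 + 4 = 16 replicates per strain, or 32 for the two wild-type strains. The only stated limit is a variation of 3 Ct. Section 5.4 places the precision specimens at about 5000 ge/mL instead.
- *LoD panel (sections 5.4, 6.2, 8.3).* 17D standard preparation only, five replicates per level.
- *Proficiency panel (section 7.3).* Three strains at three levels plus one negative make its 10 specimens, so there is one per strain at 1000. It qualifies operators before the evaluation starts.

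**The case against.** The strongest reply is that performance at 1000 ge/mL is not left untested. Section 8.3 screens assays at that limit, and the precision panel puts 32 wild-type replicates there. Under the single-hit assumption, an assay with LoD95 = 2500 would show no miss in those 32 with probability 0.698^32, about 1 in 100,000, so the failure would be seen. The precision panel also holds 1000, two higher levels and a negative, which matches the wording of the rule. The criterion may simply be misplaced, and one sentence might cure it.

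Much of this stands. It limits the consequence but does not remove the contradiction. Section 6.4 does not point to the precision panel, that panel has no detection-rate criterion, and its replicates are repeats of prepared material and not individual blinded specimens. The section 8.3 criterion rests on 17D.

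Three stronger readings are tempting, and the documents do not support them.
- A reader might infer that half of the clinical rule has no data. Two of its three clauses apply, and together they cover all 100 specimens.
- A reader might infer that the panel cannot separate good assays from poor ones. It fails an assay with LoD95 = 5000 in 64% of evaluations (100% − 36%) and one with LoD95 = 10,000 in more than 99%.
- A reader might infer that detection near the limit is never examined. It is, in the panels listed above.

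Reporting the result as sensitivity is a minor matter. Section 2.2 calls the assessment relative, and section 4.4 acknowledges that natural specimens would be preferable.

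**Conclusion.** The plan is wrong as written. The 1000 ge/mL clause of section 6.4 cannot be evaluated on the clinical panel, because 0 of 100 specimens are at that level. This rests on a count and on no model. Section 1.2 conflicts with the panel in the same way.

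The consequence is narrower than a loss of all evidence near the limit. Wild-type detection at 1000 ge/mL has no detection-rate criterion that can be applied, and the 5000 level discriminates weakly for assays that miss the limit by a factor of 2.5 (95% pass) to 5 (36% pass). Those two percentages depend on the single-hit assumption.

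It should be corrected before testing, because the rule feeds an evaluation on which WHO listing depends and the correction is cheap until specimens are spiked.

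**What to change.** Reconcile sections 1.2, 5.5 and 6.4 and Table 1 before specimens are prepared.

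**Preferred option, same 100 tests.** 20 specimens at 1000 ge/mL (10 per wild-type strain), 20 at 5000 (10 per strain) and 60 negatives. State the 1000 ge/mL rule as at least 19 of 20. Report agreement by concentration with exact intervals. The costs are:
- 20 more spiked specimens (40 instead of 20) and a second spiking level.
- The lower bound for a perfect specificity result falls from 95.5% (80/80) to 0.025^(1/60) = 94.0% (60/60).
- An assay with exactly 95% detection at 1000 fails the 19/20 rule 26% of the time (100% − 74%). The interval for 19/20 is also wide, 75.1% to 99.9%.

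**Minimum alternatives.** Either would resolve the contradiction, together with deleting the mention of a range of concentrations in section 1.2.
- Restate the section 6.4 criterion at the 5000 ge/mL level actually tested. This costs only wording but leaves wild-type detection at 1000 without a criterion.
- Link the 1000 ge/mL clause explicitly to the wild-type precision replicates. The precision concentration in section 5.4 must then be brought into line with Table 1. The rule must also say whether strains are pooled: with 16 replicates per strain no miss is allowed (15/16 = 93.75%), while 32 pooled allow one (31/32 = 96.9%; 30/32 = 93.75%).

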## 6.5 Interpretation and recording of test results

The interpretation of results for each assay under evaluation is made according to the manufacturer’s instructions. All runs and/or test results are recorded on a data sheet.
Preferably all test results are recorded and exported directly from the instrument to standardized test result worksheets for further data analysis.

A technician's analysis is made of each assay under evaluation and is completed by the operator performing the testing. This analysis comprises operational characteristics, ease of the procedure, reading and interpretation of results, clarity of manufactural instructions, as well as records of any specific difficulties encountered during the evaluation. Special attention should be paid to the instruction leaflet regarding clarity, presentation, content and safety issues in order to evaluate whether these instructions are sufficient for diagnostic laboratories in developing countries.

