# 3. Study implementation

## 3.1 Roles and Responsibilities

The performance evaluation will be exclusively conducted by the WHO Evaluating Laboratory. The laboratory will be responsible for the following:

- Ensure availability of the specimen reference panels identified below and maintain their integrity and traceability
- Update specimen inventory
- Conduct testing for the performance evaluation, only using staff with proven competence in the assays under investigation, in accordance with internationally recognized best practices
- Prepare a draft report on laboratory evaluation results, including supervision of the analysis of the data with other YF Laboratory Network members
- Ensure all source data, data analysis records and all correspondence are retained and archived in a detectable manner, for a period of at least ten years
- In addition, the following aspects are key to minimising error and maximising the value of this performance evaluation.

The Principle Investigator of the WHO Evaluating Laboratory, will assume the following responsibilities:

- The Principle Investigator will be responsible for training the laboratory personnel on the details of the evaluation protocol and on the use of each assay undergoing evaluation
- Only those personnel who have received specific training for this evaluation will participate in the evaluation
- Accurate record keeping is crucial to the success of the evaluation and the Principle Investigator will be responsible for ensuring that all data generated by the evaluation are recorded on the agreed data collection sheets, and are accurate and up to date
- It is important to plan work in advance and follow standard operating procedures as prepared and controlled by the Evaluating Laboratory
- Before starting the test run, the operator will prepare worksheets and label all tubes, dilution vessels, test devices or plates with the specimen’s unique number, as appropriate
- It is recommended that any manual transcription involved in testing is checked for correctness by a second operator.

WHO and the YF Evaluation Working Group will assume the following responilibilities:

- Technical advice to the Principle Investigator
- Technical and administrative management of the laboratory evaluation
- Review and verification of the draft report, including seeking of comments on the draft from the manufacturer/s
- Preparation and dissemination of the final reports
- Formal, authorized contacts with the manufacturers

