## 4.5 Usability Assessment

- Technicians with known skill in molecular assay performance will complete a questionnaire that include questions about the ease of use for the procedure including
- specimen and reagent preparation
- clarity of instructions for use
- record of any specific difficulties encountered or requirements

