## 7.3 Proficiency panels

A proficiency panel of 10 specimens comprised of the three YFV strains (17D, African and South American wild type strain) at high (100,000 ge copies/mL), medium (10,000 ge copies/mL) and low (1,000 ge copies/mL) concentrations and serum spiked with media from uninfected cell culture (negative control);. This panel must be run successfully for each assay by each operator before the evaluation.

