# Annex 1. Assessment of operational characteristics

Date:

Name of assay       Name of operator

| General information | | | |
| --- | --- | --- | --- |
| 1 | What is the stated intended use of the assay? |  | |
| 2 | What is the principle of assay? |  | |
| 3 | What is the target of the assay? |  | |
| 4 | What is the region of amplification targeted by the assay? |  | |
| 5 | Which extraction method was used? Provide details | Automatic  Semi-automatic  Manual | |
| 6 | What is detection method of the final product? | End-point  Real-time | |
| 7 | What is the specimen volume required to perform the test? |  | |
| 8 | Which specimen types are compatible with the assay? | Serum  Plasma  Specify anticoagulant:  Whole blood  Other  Specify:  State the specimen type used: | |
| 9 | What is the test kit size evaluated (number of tests per kit)?  Which other test kit sizes are available? | tests/kit       tests/kit | |
| 10 | Controls included:  - Decontamination (Uracil-N-glycosylase [UNG])  - Positive (provided by manufacturer)  - Negative (provided by manufacturer)  - Internal controls (added to every specimen)  - External QC specimen + monitoring (provided by external source i.e. not the manufacturer) | YES  NO  YES  NO  YES  NO  YES  NO  YES  NO | |
| Operational aspects | | | |
| 11 | Are instructions for use concise and clear for:  the assay?  the extraction platform?  the amplification platform?  - What instruction language options are available? | | YES  NO  YES  NO  YES  NO  English  French |
| 12 | What is the total number of tests per run?  How many specimens can be tested per run?  How many controls are required per test run? | | Total Tests:  Patient Specimens:  Controls required: |
| 13 | What is the necessary time to obtain first result starting after specimen preparation. | | hours;      min |
| 14 | What is the hands-on time for the technician performing the assay? | | hours;      min |
| 15 | Technical skills required of staff:  -Reconstitution of reagents/buffers required  -Calculation of dilutions  -Number of steps required | | YES  NO  YES  NO  Number of steps: |
| 16 | How many days of training (by the manufacturer) are required to perform the assay? | | days |
| 17 | What is the rate of invalid runs during the evaluation period?  What is the rate of invalid individual results over the evaluation period? | |  |
| 18 | What is the level of automation of the platform, including the extraction component? | | |

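### The leaflet is to be judged sufficient or not by operators already trained on the assay, with no rating planned before training, so gaps that training closed may go unrecorded

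*Protocol*

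**What the plan says.** Section 2.2 lists the operational characteristics of the assays among the specific objectives, and section 4.5 names clarity of the instructions for use as a usability item. Section 6.5 directs special attention to the leaflet and gives the reason: "in order to evaluate whether these instructions are sufficient for diagnostic laboratories in developing countries". The technician's analysis that contains this judgement "is completed by the operator performing the testing".

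Other sections describe that operator:

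- Section 4.5: "Technicians with known skill in molecular assay performance will complete a questionnaire".
- Section 3.1: testing is to be done "only using staff with proven competence in the assays under investigation".
- Section 3.1: the investigator is responsible for "training the laboratory personnel on the details of the evaluation protocol and on the use of each assay undergoing evaluation".
- Section 3.1: "Only those personnel who have received specific training for this evaluation will participate in the evaluation".
- Section 7.3, on the 10-specimen proficiency panel: "This panel must be run successfully for each assay by each operator before the evaluation".

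Annex 1 has one date field. Item 11 asks, yes or no, whether the instructions are concise and clear. On the same form, item 17 asks "What is the rate of invalid runs during the evaluation period" and item 38 asks how often the equipment broke down over the study period.

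**The concern.** The stated purpose concerns readers elsewhere: diagnostic laboratories that will receive the kit with its leaflet. The people who rate the leaflet have been taught the assay by the investigator and have shown that they can run it. If the leaflet leaves out a step or words it badly, and training supplies what is missing, that step may cause no difficulty in the evaluation and item 11 may still be answered yes. A yes/no item with no earlier reading to compare it with cannot reveal this.

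What is at stake is one conclusion within the usability objective: whether the instructions are good enough for laboratories that have not had this training.

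**Working it through.** There is no stated figure to reproduce and no arithmetic applies. The check is to trace who rates the leaflet, after what exposure, and when.

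1. **Who rates.** Section 6.5 assigns the analysis to the operator who performs the testing. Nothing adds a second reader, an untrained reader or a user from the target setting.

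2. **What that person has done before taking part.** Section 3.1 makes specific training a condition of participation and includes the use of each assay in that training. Section 7.3 makes a passed panel, per operator and per assay, a condition of starting the evaluation. Both are explicit.

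3. **When the form is completed.** No sentence fixes the moment at which item 11 is answered, so this step is an inference. Three features point to the end of testing:
   - The form has one date.
   - Items 17 and 38 need data from the whole evaluation period.
   - Section 6.5 includes difficulties met during the evaluation in the same analysis.

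4. **Whether another section fills the gap.** Section 6.1 is headed as a review of the instructions for use. Its content is that the product be used as instructed, that a copy go to WHO and that records be kept. It contains no assessment of the leaflet.

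5. **Which items are affected.** Item 11 and the leaflet comments of section 6.5 are judgements about the text, so prior training can change them. Item 15 is largely factual (reconstitution of reagents, dilution calculations, number of steps). Item 19, the complexity score, is worded to take account of the items above it, which include hands-on time (item 14) and invalid rates (item 17). It cannot be answered as worded before the assay has been run. Items 15 and 19 are therefore not part of the problem.

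The planned order is training, then a passed panel, then evaluation testing, then (by inference) the completed form. No step comes before training. Even if an operator filled in item 11 early in testing, the answer would still follow training and the panel.

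**The case against.** Several objections have force.

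- **Trained raters are a deliberate choice.** Section 4.5 says openly that the raters are skilled technicians. Section 1.2 gives the target as laboratories within the yellow fever network, and section 4 describes extraction kits and thermocyclers as already in place there. This stands, and no section contradicts it. It does not show that those laboratories would receive the investigator's assay-specific training.

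- **The leaflet need not suffice alone.** A reader might infer that section 6.5 tests whether a laboratory could work from the leaflet with no other help. The protocol does not say so, and item 16 asks how many days of manufacturer training are needed. The point made here does not depend on that standard.

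- **Operators keep using the leaflet.** A reader might infer that trained operators no longer rely on it. Section 6.1 requires use according to the instructions, and sections 6.5 and 7.5 require interpretation according to them. Operators can therefore still comment usefully on presentation, content and safety wording.

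- **Exposure per operator is unknown.** A reader might infer that each rater has run about 300 tests. That is the total for one assay (305 in Table 1, 310 in section 10). Section 4.1 and Table 1 spread the inter-assay runs over different technicians, and no per-operator count is given.

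- **The direction of any shift is not established.** It is plausible that training makes a leaflet seem clearer. Repeated runs may also expose faults, for instance in handling invalid results, that a first reading would miss. The documents do not settle which effect is larger.

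- **Little depends on the rating.** Item 11 has no acceptance threshold. The explicit ground for not listing an assay is the limit of detection in section 8.3. This is correct and makes the point a minor one.

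**Conclusion.** The point holds in a limited form. Training on the assay and a passed panel are explicit conditions for every rater, and no rating before them is planned. Leaflet gaps already filled by training may therefore go unrecorded, and the rating cannot carry the conclusion on sufficiency that section 6.5 attaches to it. It can carry a conclusion on clarity as judged by trained operators.

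The size of any shift cannot be taken from the documents, and its direction is plausible rather than shown. The conclusion rests on the training and panel requirements being applied as written. It does not rest on item 11 being answered at the very end. The limit of detection, analytical specificity and clinical agreement results are untouched.

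**What to change.** Move item 11 and the leaflet comments of section 6.5 to a separately dated page. Each operator completes it after first reading the instructions for use and before the investigator's training and the proficiency panel, then repeats it at the end of testing. Both ratings are reported. The conclusion on sufficiency takes account of the pre-training rating and of any gap that training had to fill. Items 15 and 19 stay at the end.

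The report should state that the raters are skilled molecular technicians. The first rating removes the effect of assay-specific training but not that of general skill, so it still does not represent less experienced laboratories directly.

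The cost is one extra page and one extra date per operator, with no additional tests, staff or kits. If this is not adopted, section 6.5 should limit its stated purpose to clarity as judged by trained operators.
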